## Abstract

**Background:**

With the opioid crisis, surging methamphetamine use, and healthcare disruptions due to SARS-CoV-2, serious injection related infections (SIRIs), like endocarditis, have increased significantly. Hospitalizations for SIRI provide a unique opportunity for persons who inject drugs (PWID) to engage in addiction treatment and infection prevention, yet many providers miss opportunities for evidence-based care due to busy inpatient services and lack of awareness. To improve hospital care, we developed a 5-item SIRI Checklist for providers as a standardized reminder to offer medication for opioid use disorder (MOUD), HIV and HCV screening, harm reduction counseling, and referral to community-based care. We also formalized an Intensive Peer Recovery Coach protocol to support PWID on discharge. We hypothesized that the SIRI Checklist and Intensive Peer Intervention would increase use of hospital-based services (HIV, HCV screening, MOUD) and linkage to community-based care: PrEP prescription, MOUD prescription, and related outpatient visit(s).

**Methods:**

This is a feasibility study and randomized control trial of a checklist and intensive peer intervention for hospitalized PWID with SIRI admitted to UAB Hospital. We will recruit 60 PWID who will be randomized to one of 4 groups (SIRI Checklist, SIRI Checklist + Enhanced Peer, Enhanced Peer, and Standard of Care). Results will be analyzed using a 2x2 factorial design. We will use surveys to collect data on drug use behaviors, stigma, HIV risk, and PrEP interest and awareness. Our primary outcome of feasibility will include the ability to recruit hospitalized PWID and retain them in the study to determine post-discharge clinical outcomes. Additionally, we will explore clinical outcomes using a combination of patient surveys and electronic medical record data (HIV, HCV testing, MOUD and PrEP prescriptions).

This study is approved by UAB IRB #300009134.

**Discussion:**

This feasibility study is a necessary step in designing and testing patient-centered interventions to improve public health for rural and Southern PWID. By testing low barrier interventions that are accessible and reproducible in states without access to Medicaid expansion and robust public health infrastructure, we aim to identify models of care that promote linkage and engagement in community care.

**Trial Registration::**

NCT05480956

## Background

With the opioid crisis, surging methamphetamine use, and healthcare disruptions due to SARS-CoV-2, the U.S. is facing a rising tide of infectious consequences of drug use [1, 2]. It is estimated that 3.6 million Americans inject drugs [3], and increasingly substance use is driving ER visits and hospitalizations. Serious injection related infections (SIRI), like endocarditis, have increased significantly in recent years with hospitalizations rising 60% to 300 admissions per 100,000 persons (2009–2018) [4, 5]. Hospitalized persons who inject drugs (PWID) often have comorbid HCV (80%); a smaller percentage have HIV (4%), but many are at high risk and would benefit from HIV prevention through PrEP [6]. Only one in 3 PWID with opioid use disorder are effectively linked to medications for opioid use disorder on discharge [7]. And, in the year following a SIRI admission, PWID often experience subsequent infections, readmissions, and death. Hence, hospitalization is a golden opportunity to engage PWID who often lack insurance and access to care [1, 8].

Admissions for SIRI generally last from two to four weeks, providing an opportunity to intervene on addiction and HIV risk and transition patients to community services [9, 10]. PWID could benefit from myriad services when hospitalized that they may not otherwise receive due to lack of access, stigma, and limited public health infrastructure in rural and poor states. HIV screening, linkage to HIV prevention and treatment, and engagement in addiction treatment (i.e., MOUD) are all feasible and acceptable services for hospitalized PWID. Yet, few health systems enable these services in the acute care setting. Many providers miss opportunities for counseling and evidence-based care due to competing demands, busy inpatient services, and a lack of awareness. An emerging body of literature on SIRI has highlighted innovative hospital approaches, such as Peer Recovery Coaches, persons with lived experience in addiction in the hospital setting [11]. However, few studies have incorporated rural and Southern people to ensure delivery of services are feasible.

The use of a “checklist” can improve provider awareness, best practice, and clinical outcomes for seriously ill patients [12, 13]. Checklists are low cost and low technology reminders to providers to ensure they deliver evidence-based services to a target population. Together with a team of physicians, social workers, and peer recovery coaches, we developed a SIRI Checklist to act as a standar[14]dized reminder to offer these patients screening for HIV and HCV, medication for opioid use disorder (MOUD), consider HIV pre-exposure prophylaxis (PrEP) and referral to appropriate community-based care. Our team also formalized an Intensive Peer Intervention whereby PWID would be contacted weekly in the month following discharge to provide support, adherence reminders, and serve as a resource related to community addiction services.

We hypothesize that it is feasible to provide a SIRI checklist and an intensive Peer support to hospitalized PWID. Further, we anticipate that the SIRI Checklist and Intensive Peer Intervention will increase use of hospital-based services (HIV, HCV screening, MOUD) and linkage to community-based care: PrEP prescription, MOUD prescription, and related outpatient visit(s).

## Study Objectives and Specific Aims

The overarching objective of this study is to test the feasibility of a SIRI checklist aimed at increasing evidence-based treatment for hospitalized PWID. We will reach this objective through the following AIMS:

Aim 1) Determine the feasibility of a pilot SIRI Checklist and Intensive Peer Intervention for hospitalized PWID to increase uptake of OUD treatment and PrEP and facilitate linkage to community-based services. Feasibility will be measured via recruitment and retention of participants, completion of each portion of the intervention (baseline surveys and follow up assessments), and ability to contact patients post-discharge for intensive Peer support and/or completion of follow up assessments. We will also evaluate the ability to extract documentation of the SIRI Checklist and Peer documentation provider notes.

Aim 2) Quantify risk behaviors in a contemporary Southern cohort of PWID and evaluate Secondary Patient-Centered Outcomes for participants enrolled in the study. We will use validated tools to survey hospitalized PWID on substances used and methods of use, HIV risk behaviors, and substance use stigma. We will also explore the preliminary impact of this low-tech checklist on evidence-based services, such as initiation of buprenorphine, PrEP, HCV screening, and referral to community care. These measures will be compared with treatment groups that do not receive the SIRI Checklist.

## Methods/Design

### Setting

We will recruit 60 participants who are hospitalized for SIRI at the University of Alabama at Birmingham (UAB) Hospital to participate in this pilot clinical trial. The UAB Health system, anchored by the 1157-bed tertiary care center of UAB Hospital, is the largest in the state, and it provides care for PWID referred from other health systems across the Southeast [4].

### Study Design

To evaluate the feasibility of the checklist and intensive peer, we will conduct a pilot randomized clinical trial of the two interventions in which participants will be randomized in a 2x2 factorial design. Process outcomes from this trial, as described in Aim 1, will be used to determine feasibility [15].

#### Aim 1: Primary Feasibility Outcomes:

In Aim 1, we will pilot a SIRI Checklist and Intensive Peer Intervention. We will assess the feasibility of this low-tech checklist and Peer intervention on linkage to evidence-based services, such as initiation buprenorphine, PrEP, and referral to community care. Study feasibility will be defined as the ability to successfully recruit and retain study participants, successful completion of baseline surveys and follow up assessments, ability to contact patients post-discharge for intensive Peer support and completion of follow up assessments, ability to extract documentation of the SIRI checklist, and Peer documentation in provider notes. Participating Addiction and Infectious Disease providers will receive a standardized survey at study completion to elucidate challenges and opportunities to improve the SIRI checklist.

#### Aim 2: Secondary Patient-Centered Outcomes:

In Aim 2, we will use validated tools to survey participants on specific substance use and behaviors, stigma, HIV risk, and preferences around care delivery. Specifically, we will use the 14-item Behavioral Risk Assessment for Infectious Diseases (BRAID) scale, which queries drug use and sexual behaviors while using drugs, and the Substance Use Stigma Mechanisms Scale (SU-SMS), an 18-item validated, theoretically-based assessment [16, 17]. The first component includes surveys that will be administered electronically via tablet in private hospital rooms to reduce social desirability bias (appendix 1) [18]. The second component will be a 3-month follow up survey to assess use of PrEP, addiction treatment, and healthcare utilization. These sessions will last 30 minutes and 45–60 minutes, respectively. Each survey session will include a $30 incentive for patients.

Preliminary treatment outcomes will be explored using hospital data, such as rates of screening for HIV and receipt of HIV prevention (PrEP).

Traditionally, research on PWID is limited by a lack of retention beyond 30 days. To test the feasibility of retaining patients in the study for 3 months, we will work with a professional company, Community Tracking Service (CTS), with expertise in identifying and conducting exit interviews in persons who use drugs as part of extramurally funded research. After three attempts to reach study participants for the exit interview, our study staff will notify our partners at CTS who will then attempt to reach the participant up to one-month post-referral. These attempts may be over phone or in-person at locations identified by participants as part of their intake survey. Open-ended questions will solicit feedback on specific aspects of the checklist or delivery that need to be addressed, edited, or removed before a subsequent randomized controlled study [19]. For participants who do not complete the exit interview, we will review the UAB and coroner data to determine if hospitalized or deceased.

To evaluate the transition to the main trial, we will utilize progression criteria around 1) recruitment and retention, 2) protocol adherence, 3) safety and adverse effects, and 4) signals of efficacy [14]. We will utilize the red, amber, green system for progression criteria [20]. (Fig. 1) For recruitment, we expect to encounter 3 to 4 eligible participants monthly, based on previous studies we have conducted within this population. Given that some of these individuals will refuse to participate in the study, we expect to enroll 2 to 3 participants each month. If we maintain recruitment of 2 or more patients per month, we expect to reach our goal of enrolling 60 participants (15 participants for each arm of the study) within 24 months. If recruitment falls below 2 patients per month, we will explore alternate methods for recruitment to improve recruitment rates. If recruitment stalls and no patients are recruited for more than two consecutive months, the trial will terminate. Retention will be determined by documenting the proportion of: participants who complete weekly calls with their peer, peer calls completed, and participants who complete the follow up survey at 3 months. The target retention rate for each of these rention progression criteria is 75% [21].

To ensure adherence to the study protocol, we will monitor patient documentation to determine whether the ShaPe “smart phrase” was utilized in patient notes. We expect that this smart phrase will be included in all participant documentation after implementation. If adherence to the study protocol falls below 80%, we will revisit the protocol with providers to determine whether further training or modifcations are necessary [21].

The third progression criterion we will employ is participant safety and adverse effects. For this criterion, we will use a Data Safety Monitor model (DSM). A DSM will be designated as an independent faculty member charged with ensuring that the safety of study subjects is protected and that the scientific goals of the study are being met. To support those purposes, the DSM will review any proposed amendments to the study protocol, perform expedited monitoring of all serious adverse events, perform ongoing monitoring of drop-outs and non-serious adverse events, determine whether study procedures should be changed or the study should be halted for reasons related to the safety of study subjects, and perform periodic review of the completeness and validity of data to be used for analysis of safety and efficacy. The DSM will also ensure subject privacy and research data confidentiality.

Finally, to evaluate signals of efficacy, we will evaluate whether participants have received the recommended services that are included in our ShaPe intervention, such as HIV and HCV screening, MOUD prescriptions, and HIV PrEP referrals. Specifically, we will evaluate whether these measures are enacted after the inclusion of the smart phrase text. This data will be collected via provider documentation and the 3-month follow-up survey with participants.

These progression criteria will be used to determine protocol adjustments to be made prior to enacting a larger study. For example, should the recruitment timeline be insufficient, we will evaluate whether the intended population is large enough for a study to be conducted and if so, how we could better identify eligible participants to be enrolled in the study. Adjustments to the smart phrase text will be made to account for under utilization in patient notes and insufficient delivery of recommended services to participants. We will also determine whether the number lost to follow-up reflects adequate usage and efficiency of CTS. In the event that these adjustments are not adequate for a larger study to be conducted, we will establish a new protocol for study.

All amendments and changes to protocol must be approved by UAB IRB before enacted.

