#### Sampling and Recruitment Procedures

Participants will be recruited following hospitalization for SIRI at UAB Hospital. Our research coordinator will meet biweekly with the Addiction Medicine social worker and/or nurse practitioner, to identify eligible PWID who express interest in study participation. The research team member will then discuss the study with those who are eligible, and if the participant expresses interest, the informed consent process will be completed (appendix 3). We will provide phones for participants who do not have access to a phone. The participant will then complete the survey used to accomplish Aim 1. Following survey completion, the participant will be randomly sorted using a 2x2 Factorial Design, into one of the four groups: SIRI Checklist, SIRI Checklist + Enhanced Peer, Enhanced Peer, and Standard of Care. Randomization will be performed in advance using blocks of n = 4 and n = 8. A total of 60 participants will be recruited, 15 per group, which is in alignment with sample size guidance for pilot and feasibility studies [24]. For incentive, patients will receive a $30 gift card at enrollment, as well as a $30 gift card at the 3-month follow up (Fig. 2).

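### The recruitment floor of 2 per month gives 48 participants in 24 months, not the stated 60; the target needs an average of 2.5 per month

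*Protocol article*

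**What the plan says.** The recruitment criterion stands in the progression-criteria text under the Aim 2 heading of the protocol article. It builds up in four steps.

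- **Supply of patients:** "we expect to encounter 3 to 4 eligible participants monthly".
- **Enrolment after refusals:** "we expect to enroll 2 to 3 participants each month".
- **The rate held to be enough:** "If we maintain recruitment of 2 or more patients per month, we expect to reach our goal of enrolling 60 participants". The sentence goes on to give the allocation and the period: "15 participants for each arm of the study) within 24 months".
- **The corrective trigger:** "If recruitment falls below 2 patients per month, we will explore alternate methods for recruitment to improve recruitment rates".

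The only other recruitment rule used during the trial is for a complete stall: "If recruitment stalls and no patients are recruited for more than two consecutive months, the trial will terminate".

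The target is the same throughout. The abstract, the Setting section and the inclusion criteria all give 60, and Sampling and Recruitment Procedures states: "A total of 60 participants will be recruited, 15 per group".

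**The concern.** One sentence gives a monthly rate, a target and a duration, and the rate multiplied by the duration does not give the target. The same rate is then the cut-off for action. A trial averaging somewhat above 2 per month would be on course by the written rule while heading for fewer than 60 participants at 24 months.

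This matters because the trial is a feasibility study. Recruitment is part of the primary outcome in the Aim 1 and Analysis sections, and it belongs to the first of the four progression criteria. With the present wording the trial could meet its stated monthly floor and miss its stated enrolment goal, and the text does not say which of the two counts.

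**Working it through.** **Inputs, all from the protocol article**

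- Target: 60 participants, 4 groups of 15 (Sampling and Recruitment Procedures).
- Rate stated as sufficient: 2 per month or more (progression criteria, Aim 2).
- Period: 24 months (same sentence).
- Expected enrolment: 2 to 3 per month (same paragraph).
- Corrective trigger: below 2 per month (same paragraph).

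**Step 1. Try to reproduce the stated 60.** Enrolment = monthly rate × months.

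| Average rate per month | Enrolled in 24 months | Months to reach 60 |
|---|---|---|
| 2.0 | 2.0 × 24 = 48 | 60 / 2.0 = 30 |
| 2.25 | 2.25 × 24 = 54 | 60 / 2.25 = 26.7 |
| 2.4 | 2.4 × 24 = 57.6 | 60 / 2.4 = 25 |
| 2.5 | 2.5 × 24 = 60 | 60 / 2.5 = 24 |
| 3.0 | 3.0 × 24 = 72 | 60 / 3.0 = 20 |

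The stated figure comes back only at 60 / 24 = 2.5 per month, which is the midpoint of the expected range, (2 + 3) / 2. It does not come back at the floor of 2.

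**Step 2. Size of the gap at the floor.** 60 − 48 = 12 participants, and 12 / 60 = 20%. Per arm this is 48 / 4 = 12 in place of 15. In time it is 30 − 24 = 6 months late.

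**Step 3. The rates affected.** Any average from 2.0 up to but not including 2.5 satisfies the floor and gives fewer than 60 at 24 months. That is the lower half of the plan's own expected range.

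**Step 4. Chance variation.** The document gives no accrual model, so I assume Poisson accrual. The probability of at least 60 enrolments in 24 months is then:

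| True rate per month | Mean count in 24 months | P(at least 60) |
|---|---|---|
| 2.0 | 48 | 5% |
| 2.25 | 54 | 22% |
| 2.5 | 60 | 52% |
| 3.0 | 72 | 93% |

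**Step 5. How the trigger behaves.** The text does not say whether the rate is a monthly count or a running average.

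- *Read as an average:* rates from 2.0 to just under 2.5 do not set it off.
- *Read month by month:* the chance of a count of 0 or 1 is e^(−λ)(1 + λ). At λ = 2.0 this is 0.1353 × 3 = 0.41. At λ = 2.5 it is 0.0821 × 3.5 = 0.29. The trigger would then fire often, and it would do so even when accrual is at the rate the target needs.

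**The case against.** The strongest reply is that the target and the period do fit the planning assumption. The expected 2 to 3 per month has a midpoint of 2.5, which gives exactly 60 in 24 months, and a phrase that admits higher rates is correct at 2.5 and above. That is true, and it limits the error to the lower end of the range. But the sentence makes 2 sufficient and the next one uses 2 as the cut-off, so the error lies where the rule operates.

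A reader might go further and infer three things that the document does not support.

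- **That the trigger would stay silent while the target is missed.** This follows only if the rate is an average or a perfectly steady count. Read month by month, it would fire in about 41% of months at a true rate of 2.0.
- **That the main trial would be planned on a rate that does not deliver.** The Analysis section evaluates the time and the number of eligible patients that recruitment required. The progression text also provides for a review of the population and of case-finding before a larger study if the timeline proves too short. A slow trial would be seen to be slow.
- **That the trial would pass its progression criterion at 2 per month.** The red, amber and green cut-offs are in Figure 1, which is not shown. They may match the text or differ from it. Different bands would not correct the sentence but would conflict with it.

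It is also fair to say that little depends on 60 statistically. The number is tied to guidance for pilot studies, and the planned analysis is descriptive with confidence intervals. With 48 participants the intervals would be wider, but no powered test would be lost.

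**Conclusion.** The inconsistency is real, and nothing in the visible text corrects it. At the rate called sufficient, enrolment at 24 months is 48 (12 per arm), 20% below the goal, and the goal is reached 6 months late. These figures are plain arithmetic on the document's own numbers. The 5% chance of reaching 60 at a true rate of 2.0 rests on the Poisson assumption.

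The consequence is narrower than it may first appear. For average rates from 2.0 to just under 2.5, the floor is met and the target missed, with no corrective step if the trigger is an average. This should be fixed because it is a misstated figure and threshold in a primary feasibility criterion. It is not a threat to the validity of the analysis.

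**What to change.** Make the rate, target and duration agree, in one of two ways.

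1. **Keep 60 in 24 months.** State the sufficient rate and the trigger as an average of 2.5 per month, judged on cumulative enrolment against 2.5 × months elapsed (15 by month 6, 30 by month 12). Set a tolerance below that line before recruitment is assessed. Without one, at a true rate of 2.5 and under the same Poisson assumption, cumulative enrolment is below the line by chance about 47% of the time at month 6 and 48% at month 12.
2. **Keep 2 per month.** Restate the expectation as 60 in 30 months, or as 48 (12 per arm) in 24 months. If 48 is chosen, the target must also change in the abstract, Setting, inclusion criteria and Sampling and Recruitment Procedures.

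In either case, say that the rate is a cumulative average and not a single-month count, and check that the bands in Figure 1 use the same figure.

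The cost is a change of wording and a stated expectation that looks slightly less favourable. No procedure or data collection changes, apart from a longer recruitment period or a smaller sample if option 2 is taken. By the protocol's own rule the change needs IRB approval.

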### Intervention

This study will test two interventions. The SIRI Checklist will build on the existing standard of care for SIRI by adding a standardized reminder to offer MOUD, HIV risk assessment, and refer to appropriate community-based care. SIRI Checklist was inspired by the iCARE checklist, developed for endocarditis in PWID, but is applicable for all PWID and will incorporate HIV prevention, harm reduction education, and linkage to care, including HCV treatment [5].

For participants who are randomized to receive the SIRI checklist, providers will receive instructions on how to insert a 5-item checklist into their documentation using a smart phrase text for ease of use and standardization (appendix 2). Because use of a checklist alone has been shown to change provider behavior, providers will not be required to perform any additional tasks other than daily documentation of the checklist. We anticipate that documentation of evidence-based services using a checklist reminder will increase the likelihood that participants will receive them.

The intensive peer intervention will include weekly calls to participants for 4 weeks following discharge. If participants do not respond, peers will make 3 attempts to reach participants at their preferred contact number.

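### The smart-phrase adherence criterion speaks of all participants, but only 30 of the 60 are randomised to the checklist; read literally, full delivery scores 50% against an 80% trigger

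*Protocol article*

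**What the plan says.** The progression criteria are set out in the protocol article under *Aim 2: Secondary Patient-Centered Outcomes*. For protocol adherence, the measure is use of the smart phrase: "we will monitor patient documentation to determine whether the ShaPe “smart phrase” was utilized in patient notes". The expected level comes next: "We expect that this smart phrase will be included in all participant documentation after implementation". The trigger comes straight after that: "If adherence to the study protocol falls below 80%, we will revisit the protocol with providers". The stated purpose of this step is to decide whether more training or changes are needed.

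The rest of the article assigns the checklist to part of the sample:

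- *Intervention*: "For participants who are randomized to receive the SIRI checklist, providers will receive instructions on how to insert a 5-item checklist into their documentation".
- *Sampling and Recruitment Procedures*: four groups, two with the checklist and two without, and "A total of 60 participants will be recruited, 15 per group".
- *Study Objectives and Specific Aims*, on the service outcomes: "These measures will be compared with treatment groups that do not receive the SIRI Checklist".

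**The concern.** Half of the participants are controls for the checklist. Smart-phrase use in their notes departs from their allocation. A criterion that expects the phrase in every participant's notes treats that departure as the desired result and treats its correct absence as a shortfall.

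This matters because the criterion is one of four that inform the move to a main trial. With the literal denominator, the score cannot separate good delivery in the checklist arms from leakage into the other arms. These call for opposite responses: the first supports the design, and the second weakens the randomised contrast. Leakage is at least conceivable here. *Standard of Care* gives Infectious Diseases and Addiction Medicine consultation to PWID admitted with SIRI, so the same services may see participants from every arm. *Intervention* also leaves the provider no extra task beyond documentation, on this ground: "Because use of a checklist alone has been shown to change provider behavior".

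**Working it through.** **Inputs**

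- Arms and size: 4 groups of 15 (*Sampling and Recruitment Procedures*). 4 × 15 = 60, which reproduces the stated total.
- Assigned to the checklist: 2 of the 4 groups, 2 × 15 = 30. Not assigned: 60 − 30 = 30.
- Threshold: 80% (*Aim 2*, progression criteria).
- Assumption: each participant is scored once, smart phrase present or absent. The article does not say whether the unit is the participant or the note.

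**Formula.** Let u be the proportion with the smart phrase among the 30 checklist participants, and c the proportion among the other 30. Three readings of adherence are possible:

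- A, all participants (the literal wording): (30u + 30c)/60
- B, checklist arms only: u
- C, agreement with allocation: (30u + 30(1 − c))/60

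**Literal reading (A)**

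1. Full delivery, no leakage (u = 1, c = 0): 30/60 = 50%, below the trigger.
2. Count needed for 80%: 0.80 × 60 = 48.
3. With all 30 checklist participants covered, the remainder is 48 − 30 = 18 non-checklist participants, and 18/30 = 60%. If u is below 1, more are needed.
4. Meeting the stated expectation (60/60) means c = 100%.

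**The readings side by side**

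| u | c | A: all 60 | B: checklist arms | C: agreement with allocation |
|---|---|---|---|---|
| 100% | 0% | 50% | 100% | 100% |
| 80% | 0% | 40% | 80% | 90% |
| 100% | 60% | 80% | 100% | 70% |
| 80% | 80% | 80% | 80% | 50% |
| 100% | 100% | 100% | 100% | 50% |

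Under A, the score rises with c. The row with 80% use in both halves meets the threshold although the arms no longer differ in checklist exposure. Under B, the threshold is 0.80 × 30 = 24 of 30 and full delivery scores 100%, but the score is blind to c. B therefore needs c reported beside it.

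**The case against.** The strongest reply is that the 80% rule never names a denominator of 60. The sentence about all participants is an expectation, whereas the trigger refers to adherence to the protocol, and that protocol reserves the smart phrase for those randomised to it. Leaving it out for a control is then adherence, and full delivery scores 100%. The same section sets a 75% target for participants completing weekly peer calls without limiting it to the two peer arms, which suggests loose drafting. The missing Figure 1 carries the traffic-light criteria and may define the denominator. All of this stands as a case about what the authors intended. It does not remove the conflict: the sentence that sets the expected level covers all participants, and no text shown narrows it. If Figure 1 does narrow it, the text still has to be brought into line.

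A reader might also infer stronger points that the documents do not support:

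- *A perfectly run trial would fail.* Falling below 80% leads only to a review with providers. The one termination rule among these criteria concerns recruitment.
- *Retraining would spread the checklist to controls.* This is speculation. A review against the *Intervention* section could equally correct misuse.
- *The team is planning a before/after roll-out.* The reference to implementation can mean the time after a given patient's providers have been instructed.
- *Contamination is likely, and nothing in the plan measures it.* The article gives no figure for its likelihood. Figure 1 is not shown, and an article may leave such monitoring to the full protocol.

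**Conclusion.** The point holds as a conflict between a stated progression criterion and the factorial design. Taken literally, with participants as the unit and all 60 as the denominator, full delivery without contamination scores 50%, and the 80% level can be reached only with the smart phrase in at least 18 of the 30 non-checklist participants. Use in the wrong arm then counts as adherence.

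The 50% figure depends on that reading. If the checklist arms were intended, the threshold is 24 of 30 and the arithmetic problem disappears, but the wording is still wrong. The consequence is a misleading adherence figure and a possibly unwarranted review, or no review when one is needed. It does not affect randomisation, safety monitoring or stopping.

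**What to change.** In the adherence paragraph of the progression criteria, replace the reference to all participants' documentation with documentation of participants randomised to either checklist arm, and attach the 80% threshold to that group explicitly (24 of 30). State whether the unit is the participant or the note. From the same note review, report smart-phrase use among the 30 participants in the Enhanced Peer and Standard of Care arms as a separate measure of contamination, with 0 of 30 expected under the allocation. Whether to set a ceiling on that measure, and at what level, is for the sponsor to decide. Check that Figure 1 uses the same denominators.

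The cost is a change of wording and a tabulation by arm. The note review is already planned, so no new data collection is needed.
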